Kenya’s modern contraceptive use among married women is 53%, with an unmet need of family planning of 18% and a total fertility rate of 3.9, as per the last DHS of 2014 [9]. The more recent PMA 2020 round 7 data from 2018 indicates a further increase in the modern contraceptive prevalence rate (mCPR) to 60.7% and a reduction in unmet need to 13.8% [10]. Despite the improvement in contraceptive use, discontinuation rates have remained higher over the last three decades with one out three women discontinuing use by 12 months [9]. Contraceptive continuation rates has been suggested as a useful summary measure of the overall effectiveness of program services in enabling clients to sustain contraceptive use even though they may switch from one method to another [11, 12]. The PMA 2020 round of surveys have shown that there is still a huge gap in provision of quality of family planning services at the health facility and community levels, with only 67% of the women informed of other methods, 59% counseled on side effects, and 54% told what to do when they experience the side effects, thus presenting missed opportunities for provision of quality family planning services that might promote continuation or method switching [10].

In Kenya, as in other lower-middle income countries, the national health management information system does not monitor contraceptive continuation at the facility level, as the data capture mechanism is not longitudinal. More so, within the health system, only users of reversible methods, including implants and IUDs, go back to a facility, since they require a clinical intervention during removal of these methods. Users of short-term methods, like condoms, pills, and injectables, simply fail to turn up for their next appointment for resupply. Therefore, tracking contraceptive discontinuation and method switching is limited to use of survey data such as a DHS that collects calendar data on women’s history of contraceptive use.

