##### Sample size

This phase is powered to detect a 10 percentage point difference in the primary outcome of interest— reductions in contraceptive discontinuation rates at 12 months, between baseline and endline levels with a 95% confidence interval and a power of 80%. For the purpose of the sample size calculation, Kenya DHS data was used for the current contraceptive discontinuation rate of 31% [9]. Further, the sample size is adjusted to account for a 30% attrition rate due to potential dropouts and loss of clients during follow-up through the four waves of data collection up to 24 months and a design of effect of 1.5 due to cluster sampling. This results in a total sample size of 508, which is doubled for the overall study (for the two counties), leading to 1016 women. Proportionate to size is used to allocate the sample size for each of the 10 facilities based on the current family planning caseload. Additionally, the current method mix for the two counties further determines the sample for each modern contraceptive method.

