##### Outcomes

The primary outcome of this study is the contraceptive discontinuation rate among the family planning users at 12 months. Participants will be considered to have discontinued if they report not using their baseline method during the follow-up interviews. Participants who discontinue use of the method used at the time on enrollment and initiate use of different method within one month will be considered to have switched methods. Other secondary outcome measures include discontinuation at 3, 6, and 24 months; the method information index [11] will be used as a proxy for quality of family planning counseling.

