##### Data analysis

Quantitative data will be collected on RedCap [17] and cleaned before analysis to ensure completeness. Descriptive analysis of quantitative variables will be done using measures of central tendency (mean, median) and measures of dispersion (range, standard deviation), as appropriate. Descriptive statistics will be used to assess contraceptive discontinuation, including switching. Pearson’s χ2 or t test, where appropriate, will be used for univariate analyses to compare characteristics of women who continued and discontinued their initial contraceptive method. Multivariate analysis will be implemented for variables that will be significantly associated with contraceptive continuation at bivariate analysis. The time to event for this survival analysis will be calculate from method initiation to the time point when the participant reports discontinuation with her baseline method. Censoring will be done for clients lost to follow-up and those reporting discontinuation of their baseline method. Contraceptive discontinuation rates will be calculated using the Kaplan Meier survival function. Cox proportional hazard regression model will be used to estimate hazard ratio for risk of contraceptive discontinuation for independent predictors of discontinuation. The level of significance will be set at a *p*-value < 0.05. For qualitative data, the approach for data analysis will be similar to what has been presented above under the formative assessment.

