### Ethical considerations

Written informed consent will be obtained for all study participants. All married adolescents and those who have previously given birth will be considered emancipated/mature minors and eligible to give consent themselves. All respondents will be informed about the objectives, procedures, benefits, and risks of the study through the process of obtaining informed consent. There is some minimal risk associated with participating in the prospective cohort study especially among women taking a family planning method without the knowledge of their partners, hence, follow-up interviews might expose them. Information regarding the follow-up interview will be communicated to the participants at the time of consenting during enrolment. Participants will be asked whether they will have any concerns about their privacy regarding the follow-up interviews. During the follow-up interviews, the research assistants will establish whether the participants are in a safe environment where they can talk freely. The English questionnaire will be translated into and back-translated from Dholuo for Migori, Kamba for Kitui, and Swahili for both counties. All research assistants engaged in this study will be recruited based on prior experience in administering questionnaires. They will be trained on study design and procedures and ethical consideration, including the need for confidentiality, anonymity, consent, as well as their role as data collectors and how to complete the data collection tool. Field testing of the tool among a similar group of study participants will be undertaken prior to the study to identify potential issues that needs modification. Monitoring visits will be made by the principal investigator and co-investigators to ensure fidelity to the study protocol.

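### The 12-month discontinuation rate treats women lost to follow-up as if loss were unrelated to stopping; the rate may be biased in either direction, and the stated analysis does not show by how much

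*Protocol article*

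**What the plan says.** - Outcomes: "The primary outcome of this study is the contraceptive discontinuation rate among the family planning users at 12 months". A woman counts as having discontinued when she reports at a follow-up interview that she no longer uses her baseline method.
- Data analysis: "Censoring will be done for clients lost to follow-up". The sentence in full reads "Censoring will be done for clients lost to follow-up and those reporting discontinuation of their baseline method", and the next one "Contraceptive discontinuation rates will be calculated using the Kaplan Meier survival function". No weighting of the Kaplan-Meier estimate is mentioned.
- Participant recruitment and Participant follow-up: the interviews at 3, 6, 12 and 24 months are by phone. Loss is declared after three failed attempts in a round, and consent is asked for again each time.
- Sample size: "the sample size is adjusted to account for a 30% attrition rate due to potential dropouts and loss of clients during follow-up", and this runs "through the four waves of data collection up to 24 months". The reference rate is 31%, from the Kenya DHS, and the target difference is 10 percentage points.
- Study design: a single group, so there is no concurrent control.

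**The concern.** Kaplan-Meier lets the women still in contact stand in for those who have left. This is unbiased only when leaving carries no information about stopping. In this cohort the event can be seen only through the contact that is lost: a woman who stops and is then never reached again cannot become an event. Renewed consent at each round also makes loss partly a woman's own choice.

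The estimate is to be read against an external 31%, and the Dissemination section intends to show how the discontinuation rate has changed. With one group, no comparator would share the same loss and so reveal the bias. If stoppers are the harder ones to reach, the rate is too low and part of an apparent reduction comes from follow-up. If continuing users are the harder ones to reach, the rate is too high and a real reduction is understated.

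**Working it through.** **1. How the 30% enters the plan.** With 31% against 21%, one-sided 5%, 80% power and pooled variance, mean 0.26:

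n = [1.645·√(2·0.26·0.74) + 0.842·√(0.31·0.69 + 0.21·0.79)]² / 0.10² = 237 per group.

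237 × 1.5 / 0.70 = 507.9, i.e. 508, and doubling gives 1016. The plan's figures reproduce. The sidedness is inferred (two-sided gives 301 × 1.5 / 0.70 = 645). The 30% is used only to inflate recruitment. That restores precision but does not remove bias.

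**2. Loss by month 12.** The 30% is a 24-month total and its timing is not given. At a constant loss rate, L = 1 − 0.70^(12/24) = 16.3%. This is an assumption.

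**3. Model.** Reported discontinuation is taken as the event. Kaplan-Meier reads 21% (the planned 31% less 10 points), with constant hazard. A lost woman is censored at her last completed contact, t = 0, 3 or 6 months. After t her hazard is m times that of retained women. The documents give no m, so a range is shown.

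- Shares lost after contact at 0, 3 and 6 months: w = 0.0436, 0.0417, 0.0780 (sum 0.163).
- Probability that such a woman stops by month 12: F(t, m) = 1 − 0.79^{[t + m(12 − t)]/12}.
- True rate = (1 − L)·0.21 + Σ w·F(t, m), where (1 − L)·0.21 = 0.1757.

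| m | F(0) | F(3) | F(6) | True rate | True minus Kaplan-Meier |
|---|---|---|---|---|---|
| 0.5 | 0.111 | 0.137 | 0.162 | 19.9% | −1.1 points |
| 1 | 0.210 | 0.210 | 0.210 | 21.0% | 0 |
| 1.5 | 0.298 | 0.277 | 0.255 | 22.0% | +1.0 |
| 2 | 0.376 | 0.338 | 0.298 | 22.9% | +1.9 |
| 3 | 0.507 | 0.445 | 0.376 | 24.6% | +3.6 |

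Example, m = 2: 0.1757 + 0.0436·0.376 + 0.0417·0.338 + 0.0780·0.298 = 0.229.

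**4. Bounds and tipping point at 16.3% loss.**

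- No lost woman stopped: 0.837·0.21 = 17.6%.
- Every lost woman stopped: 0.1757 + 0.163 = 33.9%.
- Share of lost women who must have stopped for the true rate to be 31%: (0.31 − 0.1757)/0.1633 = 82%. Solving the formula in step 3 for 31% gives m of about 10.7.

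These concern the point estimate. Sampling error would make a reduction uncertain sooner.

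**5. A second mechanism.** Suppose instead that a woman who has stopped since the last call is r times as likely to be unreachable at the next as a continuer, whose chance of loss is q per call. With p the probability of stopping in the interval, the Kaplan-Meier step is p(1 − rq) / [p(1 − rq) + (1 − p)(1 − q)]. Set q so that 30% are lost by 24 months. A true 21% then reads 21.9% (r = 0.5), 21.0% (r = 1), 19.5% (r = 2) or 18.2% (r = 3). A true 31% reads 32.2%, 31.0%, 29.0% or 27.4%. The bias is of the same order and again takes either sign.

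**The case against.** Censoring lost women in Kaplan-Meier is standard, and the same remark fits most cohorts with attrition. The design also limits loss: women without a phone they control are excluded, participants must accept four contacts, and three attempts are made per round. Sensitivity analyses for loss may sit in a full protocol or SAP that is not shown. All of this stands. The point is therefore about the limits of the estimator that the article fixes, and the absence of a sensitivity analysis is not counted as an error.

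Four stronger readings are tempting, and the documents do not support them:

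- *That the protocol itself describes stoppers as dropping out of contact.* The Background says "Users of short-term methods, like condoms, pills, and injectables, simply fail to turn up for their next appointment for resupply". That concerns missed clinic resupply and explains why routine facility data cannot track discontinuation. Missing a resupply visit is not missing a study phone call.
- *That the rate is likely too low.* The Ethical considerations section sees risk "especially among women taking a family planning method without the knowledge of their partners, hence, follow-up interviews might expose them". These women are current users. If they avoid calls, continuers are lost and the rate is too high.
- *That 30% are missing at the primary time point, three times the target effect.* The 30% runs to 24 months, and a loss fraction is not commensurable with a risk difference. All 30% falling in year 1 is an extreme case.
- *That the Cox hazard ratios are biased for predictors tied to loss, such as method or county.* A Cox model allows censoring to depend on covariates that it includes. Bias needs loss to depend on stopping given those covariates, which nothing here shows.

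**Conclusion.** The concern holds as a risk of informative censoring in the primary 12-month rate, with direction unknown. At about 16% loss by month 12, a hazard in lost women of 0.5 to 3 times that of retained women moves the true rate from 1.1 points below to 3.6 points above the Kaplan-Meier reading. That matters against a 10-point target but falls well short of erasing it, which would need about 82% of lost women to have stopped. The size rests on three assumptions that the documents do not supply: constant loss and stopping rates, the value of the multiplier, and a Kaplan-Meier reading of 21%.

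The sentence on censoring also lists women who report discontinuation, who are the events. That is a separate matter. Correcting it would leave this point in place.

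The planned analysis need not be abandoned. This is an inexpensive improvement that makes clear how far a comparison with 31% depends on an assumption about women not reached.

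**What to change.** In the Data analysis section:

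- Keep the unweighted Kaplan-Meier estimate and report beside it an inverse-probability-of-censoring-weighted one. Build the weights from data already collected: method, county or facility, age, fertility preference, and partner and decision-making items at baseline, plus side effects and satisfaction at the last completed call. Women lost before the 3-month call contribute baseline variables only.
- Weights correct only for measured predictors of loss. So pre-specify a delta analysis of the 12-month rate with multipliers on both sides of 1 (for example 0.5, 1.5, 2 and 3), and the bound that counts every lost woman as having stopped.
- State any reduction against 31% together with the multiplier at which it disappears, and report the actual loss by month 12.

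Cost: analysis wording and modest programming, with no new data or participants. The weighted estimate will have a slightly wider confidence interval, and the rate may turn out less favourable.

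### The survival analysis paragraph treats reported discontinuation of the baseline method both as the event and as a reason for censoring

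*Protocol article*

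**What the plan says.** The Outcomes section of Phase 2 sets the endpoint: "The primary outcome of this study is the contraceptive discontinuation rate among the family planning users at 12 months". It then defines the event: "Participants will be considered to have discontinued if they report not using their baseline method during the follow-up interviews". Women who stop the baseline method and "initiate use of different method within one month will be considered to have switched methods".

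The Data analysis section of Phase 2 measures time from method initiation "to the time point when the participant reports discontinuation with her baseline method". The sentence after that is the censoring rule: "Censoring will be done for clients lost to follow-up and those reporting discontinuation of their baseline method". The next two sentences name the estimators: "Contraceptive discontinuation rates will be calculated using the Kaplan Meier survival function", and "Cox proportional hazard regression model will be used to estimate hazard ratio for risk of contraceptive discontinuation".

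No other section corrects the censoring rule or limits it to a subgroup.

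**The concern.** In a time-to-event analysis each woman's follow-up ends either in the event or in censoring. Here the event and one of the two censoring reasons are described in almost the same words, and both refer to the baseline method. An analyst who follows the censoring sentence codes every woman who stops as censored. An analyst who follows the sentence before it codes the same woman as an event.

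The rule governs the Kaplan-Meier estimate of the primary outcome at 12 months, the secondary rates at 3, 6 and 24 months, and the Cox analysis that serves the objective on predictors of discontinuation.

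**Working it through.** **1. The statements side by side**

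| Place | Role given to stopping the baseline method |
|---|---|
| Outcomes, definition of discontinued | Event |
| Data analysis, end of time to event | Event |
| Data analysis, censoring sentence | Censoring |
| Data analysis, Kaplan-Meier sentence | Event |
| Data analysis, Cox sentence | Event |

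Four statements treat it as the event and one treats it as censoring. Switchers do not remove the conflict, because they too have stopped the baseline method.

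**2. The censoring sentence applied literally**

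The Kaplan-Meier estimate is S(t) = product over event times of (1 − d_j/n_j). If every discontinuation is censored, d_j = 0 throughout, so S(t) = 1 and the discontinuation rate 1 − S(t) is 0% at every time point. The Cox partial likelihood has one factor per event. With no events it has no factors, and no hazard ratio can be estimated.

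**3. How many events are at issue**

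Inputs from the Sample size section: reference rate 31%; difference to detect 10 percentage points, hence 21%; 1016 women; 30% attrition over the four waves up to 24 months; design effect 1.5.

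The plan's own sample size reproduces: a pooled two-proportion formula for 31% against 21%, 80% power and one-sided 5% gives 237, and 237 × 1.5 / 0.70 = 507.9, so 508, doubled to 1016. This does not depend on the censoring rule.

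Full follow-up to 12 months:
- at 31%: 1016 × 0.31 = 315
- at 21%: 1016 × 0.21 = 213

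With loss. Assumptions: constant hazard; 30% lost evenly over 24 months, so 3.75%, 7.5% and 15% lost by months 3, 6 and 12; a discontinuation is seen only if the next interview is completed.

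At 31%, S(3) = 0.69^0.25 = 0.9114, S(6) = 0.69^0.5 = 0.8307, S(12) = 0.69:
- months 0–3: 0.0886 × 0.9625 = 0.0853
- months 3–6: 0.0807 × 0.925 = 0.0747
- months 6–12: 0.1407 × 0.85 = 0.1196
- sum 0.2795; × 1016 = 284

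At 21%, S(3) = 0.79^0.25 = 0.9428, S(6) = 0.79^0.5 = 0.8888, S(12) = 0.79:
- months 0–3: 0.0572 × 0.9625 = 0.0551
- months 3–6: 0.0540 × 0.925 = 0.0499
- months 6–12: 0.0988 × 0.85 = 0.0840
- sum 0.1890; × 1016 = 192

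As a check, one simulated cohort of 1016 (constant hazard giving 31% at 12 months, 30% lost by 24 months, the planned interviews) gave 265 events by month 12 and a Kaplan-Meier rate of 29.6% with discontinuation as the event, against 0% under the literal rule. The 265 is a single random draw.

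**4. Why the repair must mention switchers**

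Two repairs are plausible: the clause was meant for women still using the method, or for switchers. They estimate different quantities. The article gives no switching share, so the share is an assumption here. If a constant share s of stoppers is censored as switchers and the rate for all stoppers is 31%, the Kaplan-Meier estimate becomes 1 − 0.69^(1−s):

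| Assumed share s | 12-month estimate |
|---|---|
| 0% | 31.0% |
| 10% | 28.4% |
| 20% | 25.7% |
| about 36% | about 21% |
| 50% | 16.9% |

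At a share of about 36% the choice of definition alone moves the estimate by the 10 points that the study is sized to detect.

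**The case against.** The strongest reply is that the intended event is plain. The sentences on both sides of the censoring rule, and the Outcomes section, treat discontinuation as the event, so any analyst would read the clause as a slip. That stands. A reader might infer that the primary analysis will in fact have no events and report 0%. The documents do not support that: zero events is only the literal consequence of one sentence against four others, and such a result would be noticed at once. The planned descriptive statistics and the χ² or t tests comparing women who continued with those who discontinued do not depend on the censoring rule.

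A reader might also infer a hidden bias in favour of the intervention, from discontinuers being censored in part. Nothing in the article suggests that the rule would be applied in part. The switching table above shows what an unstated choice could do; it is not evidence that the choice has been made.

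It would also be tempting to fault the rule for not listing women still on their baseline method at the end of follow-up. An article commonly leaves that detail to the full protocol or analysis plan, so it is not part of the finding. Nor should the whole 30% attrition be placed within the first 12 months when counting events, because the Sample size section spreads it up to 24 months.

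What the reply does not remove is the contradiction. The article states a censoring rule for its primary estimator, the rule is wrong as worded, and the text does not show which group was meant. The Outcomes section counts anyone off her baseline method as discontinued and then classes switchers separately. The Background describes discontinuation as abandonment while at risk of an unintended pregnancy, and continuation as something that can include a change of method. Both repairs therefore remain open.

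**Conclusion.** The point holds as an internal contradiction in the Data analysis section, probably a drafting slip, on the estimator of the primary outcome. Read literally, the rule gives 0 events, a 0% rate at all four time points and no estimable Cox model. With discontinuation as the event, about 315 (31%) or 213 (21%) events are expected by 12 months with full follow-up, and about 284 or 192 with attrition. The latter pair rests on a constant hazard, even loss over 24 months and detection only at interviews. The sample size is not affected. The wording should be corrected before outcome data are analysed, because the choice between the plausible repairs changes what the primary rate measures.

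**What to change.** In the Data analysis section, delete the second limb of the censoring sentence, the one that names women who report discontinuing. In its place state that:

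- the event is stopping the baseline method, as the Outcomes section defines it;
- women still using the baseline method, and women lost to follow-up, are censored at their last completed interview;
- switchers count as events for the primary rate, which is what the Outcomes definition implies. If the authors intend otherwise, the Outcomes and Data analysis sections need to be reconciled and the chosen definition stated in both.

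The cost is a few lines of wording. No new data are needed: the follow-up questionnaire already asks about baseline method use and about the timing of discontinuation or switching.

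### The sample size allows for clustering with a design effect of 1.5, but the named analyses carry no clustering adjustment, so uncertainty in the 12-month rate and in facility-linked predictors would be understated

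*Protocol article*

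**What the plan says.** The Sample size section of the protocol article takes a 31% discontinuation rate from the Kenya DHS and a 10-point difference, then adjusts for 30% attrition and for "a design of effect of 1.5 due to cluster sampling". This gives 508 women, doubled to 1016 for the two counties. On where the women come from it says "Proportionate to size is used to allocate the sample size for each of the 10 facilities", by family planning caseload.

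The Data analysis section names four methods. Pearson's chi-square or the t test "will be used for univariate analyses to compare characteristics of women who continued and discontinued their initial contraceptive method". Variables significant at that step go into the multivariable analysis. Discontinuation rates come from the Kaplan-Meier function. For predictors, "Cox proportional hazard regression model will be used to estimate hazard ratio for risk of contraceptive discontinuation for independent predictors of discontinuation". The significance level is 0.05.

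That section mentions neither facility nor clustering, and names no variance estimator. The primary outcome, in the Outcomes section, is the discontinuation rate at 12 months.

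**The concern.** The two sections treat the same data differently. The first enlarges the sample by half because women from the same cluster are expected to resemble one another. The second names methods which, in their ordinary form, treat the women as independent. If they are run in that form, the allowance for clustering is lost when uncertainty is calculated.

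Two results are exposed. One is the overall 12-month rate, which carries the full design effect. The Dissemination section intends to show how this rate has changed, so its uncertainty matters. The other is any predictor that varies mainly between facilities. County is the clearest case: the Study setting section wants to learn how the two counties' differing method mixes influence discontinuation. The bivariate tests also decide which variables enter the multivariable model, so a false positive there is carried forward.

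**Working it through.** **1. Is the design effect really in the sample size?** Inputs from the Sample size section: p1 = 0.31, p2 = 0.31 − 0.10 = 0.21, power 80%, design effect 1.5, attrition 30%. The pooled two-group formula is n = [z_α√(2p̄q̄) + z_β√(p1q1 + p2q2)]² / 0.10², with p̄ = 0.26. At one-sided 5% it gives 237.

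- With the design effect: 237 × 1.5 / 0.70 = 507.9, i.e. 508; doubled, 1016. This is the plan's figure.
- Without it: 237 / 0.70 = 338.6, i.e. 339.

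So the inflation was applied. (A two-sided test would give 301 × 1.5 / 0.70 = 645. How a one-sided calculation fits the section's mention of a 95% confidence interval is a separate question and does not affect this one.)

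**2. What correlation does 1.5 imply?** With facility as the cluster, the average size is 1016 / 10 = 101.6. From DEFF = 1 + (m − 1) × ICC, ICC = 0.5 / 100.6 = 0.005. With 70% retained (about 71 per facility), it is 0.5 / 70.1 = 0.007.

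**3. Quantities that carry the full design effect.**

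- Ratio of ordinary to correct standard error: 1/√1.5 = 0.816, i.e. about 18% too small.
- True level of a nominal 5% two-sided test: 2 × [1 − Φ(1.96/√1.5)] = 0.110.
- Coverage of a nominal 95% interval: 1 − 0.110 = 0.890.

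Binomial half-widths around 31% illustrate the scale. With all 1016 women, 1.96 × √(0.31 × 0.69 / 1016) = 2.8 points, and × √1.5 = 3.5. With 711 women (70% of 1016), they are 3.4 and 4.2. Neither pair is the exact precision of the primary estimate: the 30% attrition covers 24 months, and Kaplan-Meier uses the earlier data of women lost later.

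**4. Predictors.** A simulation used 10 facilities of 100 women, a 31% rate, an outcome ICC giving a design effect of 1.5, an ordinary two-proportion test at 5%, and 4,000 replicates.

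| Predictor | Rejection rate under no effect |
|---|---|
| Facility-level (5 facilities against 5) | 11.0% |
| Woman-level, ICC 0.2 across facilities | 6.1% |
| Woman-level, ICC 0.05 | 4.9% |
| Woman-level, ICC 0 | 4.9% |

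Coverage of the ordinary 95% interval for the overall rate was 89.7%, in line with step 3.

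**5. Sensitivity.** The documents give no ICC, so the range below is an assumption (101.6 women per facility, full design effect).

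| ICC | Design effect | True level of a nominal 5% test |
|---|---|---|
| 0.001 | 1.10 | 6.2% |
| 0.005 | 1.50 | 11.0% |
| 0.01 | 2.01 | 16.6% |
| 0.02 | 3.01 | 25.9% |

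**The case against.** The strongest reply is that the article is silent rather than wrong. It names estimators, not variance formulas. Kaplan-Meier and Cox can both be run with clustered variance, and a condensed article may leave that to an analysis plan that is not shown. This stands to the extent that a reader might infer the plan declares the women independent, and the text does not say that. It does not dispose of the point. The article itself raises clustering, then lists its methods without it. Pearson's chi-square and the t test in particular are procedures for independent observations, and their cluster-adjusted counterparts are different procedures.

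A second reply is that most baseline items (socio-demographic characteristics, fertility preferences, decision-making) are measured on the woman. This also stands. A reader might infer that every p-value in the study is compromised. Step 4 does not support that: tests of predictors that vary mostly within facilities stay close to 5%.

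Third, the article says cluster sampling without naming the cluster, allocates by caseload so that about 102 per facility is only an average, and uses 1.5 as a planning allowance. All true. Facility is the natural reading, and the 11% and 89% are conditional on that allowance.

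Finally, the Data analysis section mentions no confidence intervals, and the estimated rate itself hardly depends on the choice of variance. That limits the seriousness, but a primary rate that is to be set against a reference needs a sound measure of its uncertainty.

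**Conclusion.** The mismatch is real. The clustering allowance is in the sample size and absent from the named analyses. If these are run in their ordinary form and the design effect is 1.5, standard errors for the overall 12-month rate and for facility-level or strongly facility-linked predictors are about 18% too small, with about 89% coverage and about 11% type I error. Predictors that vary mostly within facilities sit at about 5 to 6%.

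The figures rest on facility as the cluster, on the plan's own design effect, and, for predictors, on a simulation with equal facility sizes and a two-proportion test in place of Cox. Point estimates are largely unaffected and the study is a single-group cohort, so this is worth correcting before analysis but does not undermine the design.

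**What to change.** In the Data analysis section, name the facility as the cluster and carry it through:

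- **Kaplan-Meier rates:** report intervals from a facility-clustered variance, for example a facility jackknife.
- **Bivariate tests:** use cluster-adjusted versions, for example a Rao-Scott chi-square and an equivalent clustered comparison of means.
- **Cox model:** use facility-clustered robust variance or a shared facility frailty.
- **Few clusters:** with only 10 facilities, add a small-sample correction, for example a t reference on about 8 or 9 degrees of freedom, because uncorrected robust variances are unreliable with so few.
- **County:** keep it as a covariate. Stratifying the Cox model by county would remove the county hazard ratio that the Study setting section's aim calls for.

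The cost is a few sentences and options in standard software, with no new data or change to recruitment. The price is somewhat wider intervals (about 22% at a design effect of 1.5, since √1.5 = 1.22, before the small-sample correction) and less power for facility-level predictors.
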